### Harms

Solicited and spontaneously reported adverse events and other unintended effects of the trial interventions or trail conduct will be managed by the Project Management team. This will be achieved through prior planning to mitigate potential harmful outcomes, and the availability of the Project Management team to address concerns and issues as they arise. For example, some of the questions in the CGA have the potential to cause distress to participants, as some questions ask the participants about possible negative life events they may have experienced. To mitigate and manage potential harmful outcomes for participants partaking in a CGA, researchers administering the CGA will be trained to follow a protocol for monitoring participant distress levels, as well as, reporting guidelines to follow in such cases. For example, dependant on the circumstances, it may be necessary for the researcher to consult with the participants GP who can then organise a referral to a psychologist, or perhaps, in a different circumstance, it may be appropriate to provide the participant with information about support services available in the local area.

### Consent

Organisational consent will be sought from the ACCHSs for participation in the research project, including for the audits carried out as part of a quality assurance process. Individual informed consent will be sought from ACCHS staff participating in the co-design and evaluation of the best-practice model of care. Individual informed consent will also be sought from the clients, carers and family members participating in the CGA, this will be achieved by providing study participants with a Plain Language Statement that clearly outlines the study processes (refer to Appendix 2 Plain Language Statement).

For individual consent processes, interpreters will be used as required. Some of the people invited to take part in the project will have dementia or other forms of cognitive impairment. If, as determined by a trained clinician, a person does not have capacity to give consent for participation in the detailed assessment and record linkage, consent will be sought from the carer, next of kin or a statutory health attorney/guardian.

### Project evaluation

#### Process evaluation

A mixed methods approach will be used for the process evaluation of the implementation [43]. Fidelity, dose and reach of the intervention will be measured and evaluated by a project-appointed sub-committee.

Qualitative data for the process evaluation will be collected from all sites during the study. Data collection will include:
Interviews with ACCHS staff at multiple time points during the implementation phase of the study to capture experiences of the intervention. Interview participants will be recruited via purposive sampling, to provide a representative sample of different roles within the health service (eg. GPs, nurses, AHWs, administrative staff, allied health staff) levels of exposure to (and possibly attitudes towards) the implementation;Project research staff notes documenting observations made during visits to ACCHSs and other contact with ACCHS staff (including phone calls and emails);Any feedback from AWCs regarding the implementation.

The iPARIHS framework will be used to guide the implementation. As such, all data collected for the process evaluation will focus on the characteristics of the implementation of the best-practice model of care for cognitive impairment and dementia (the innovation), who is affected by it (the recipients) and how they are affected by it, the inner and outer contexts within which the model of care is being implemented, as well as the facilitation of the implementation.

#### Health economic analysis

An economic evaluation will be conducted as part of this study. Best-practice methods will be utilised to undertake a cost-utility analysis of the intervention with quality of life as measured and valued by the EQ-5D as the primary outcome measure [44]***.*** Resource use associated with the development and implementation of the Let’s CHAT model of care (including staff time spent developing and administering the program, consumables, software development and others) will be carefully documented, measured and valued.

### Quality Assurance & Data Monitoring

A Data Monitoring Committee (DMC) has been established. The DMC is not independent from the study organisers and is composed of the central management team. The DMC will undertake check and data cleans periodically for all study sites to ensure data collection adheres to the study protocol. Spot checks will also be undertaken on a semi-regular basis by a member of the DMC to assess the reliability of the data collected from the different ACCHSs involved in the study. Quality assurance of data collected in this study will be validated through electronic checks via the REDCap system (used for data collection in this project). These data monitoring processes will ensure that the quality and completeness of the data will be maintained over the course of the project.

### Analysis and sample size

#### Analysis

Statistical analysis will be conducted using generalised linear mixed models (GLMM) where variation between clusters will be modelled as a random intercept effect and, nested within these, time will be treated as a random coefficient effect. No single model can assess all the possible time-related effects that may be of interest and to this end up to four different model configurations will be used as outlined in Twisk et al. [45].

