## Methods

### Design

This research project has adopted a stepped wedge cluster randomised controlled trial design with 12 clusters (ACCHSs) across four states of Australia. This method was chosen for pragmatic and ethical reasons - each cluster will experience the intervention over the course of the study, contamination of the groups prior to intervention is minimised due to geographic separation, and the design minimises the difficulties of implementing a program simultaneously over large distances [26, 27].

In the context of Indigenous research, a community participatory approach is essential to ensure the community, service providers and stakeholders are involved at all stages enabling successful translation into sustainable outcomes [28]. The CQI “plan, study, do, act” cycle will be utilised in combination with the i-PARIHS framework with the purpose of being a practical and familiar way to engage staff in practice change [29, 30]. The clinical and support staff within each ACCHS will be invited by the research staff to co-develop and participate in the implementation phase of the project – consisting of staff education and resource development. Additionally, staff from each ACCHS and local Community members will be recruited to act as project Ageing Well Champions (AWC) – co-researchers and leaders for change [24]**.** The primary role of AWCs will be to assist with implementing the Let’s CHAT Dementia model of care. They will be selected by ACCHS staff based on prior experience working with older Aboriginal and Torres Strait Islander Australian peoples. A protocol will be developed to outline the role of the champions.

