### Setting

The study will be undertaken in North Queensland, New South Wales, Victoria and Western Australia with recruitment of three ACCHS in each state. Each health service (cluster) will be randomised to determine the sequence of commencement of education and resource provision (the implementation phase) and the ACCHSs will enter the implementation phase of the study at six-monthly intervals. Randomisation will be carried out by a statistician external to the project team. One ACCHS per state will begin the implementation phase at a time. Allocation concealment will be ensured until the second group of ACCHSs enters the intervention phase, at which time all ACCHSs will be aware of their allocation sequence. Blinding of trial participants (ACCHSs) and data collectors will not be possible, since both groups will be aware of and possibly engaged in the implementation activities taking place once a health service enters the intervention phase. However, the research team plans to recruit external outcome assessors to check data samples. Table 1 (below) outlines the expected timeline for each phase of the project.

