### Methods: data collection, management and analysis

#### Data collection and management

##### Medical record audit

A specific audit tool has been developed to collect data from eligible ACCHS clients 50 years and over (see Table 2 for data collection timetable). The audit tool documents clients’ dementia risk profile, any assessments or investigations relating to cognition, new diagnoses of dementia and CIND as well as describing the care pathways of any cognitively impaired clients, including referrals, hospitalisations and mortality. Data will be collected by trained research assistants using REDCap; an online, secure, password protected, web-based data collection support tool. Data will be de-identified with a unique identifier code allocated to each participant to enable linking between successive audits, with data re-identifiable only in the clinical setting. Audits will be completed either by trained research assistants or ACCHS staff, depending on each service’s preferences.

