**Table Taba:** 

Data collection	Baseline	6 monthly^a^	12 monthly^a^
Audit tool: demographic data & dementia mapping	X	X	X
Documentation of dementia or CIND (audit tool)	X	X	X
Audit documenting best practice	X	X	X
Participant: Comprehensive Geriatric Assessment	X		X
Carer: Outcomes	X		X
Health professionals: Process data	X	X	X

^a^6 monthly collection of data will continue from baseline to 36 months

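### If the random time effect is a linear slope, irregular audit-to-audit variation within a service has no term in the stated model, and the type I error can exceed 5%

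*Protocol article*

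**What the plan says.** Under Analysis, the protocol article describes the random part of the model: "variation between clusters will be modelled as a random intercept effect and, nested within these, time will be treated as a random coefficient effect". It adds that no single model can cover every time-related effect, so "up to four different model configurations will be used as outlined in" a cited source. None of these configurations is named as primary, and no separate service-by-audit random effect is mentioned.

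The layout comes from two other places. Setting has three services in each of four states, states that "the ACCHSs will enter the implementation phase of the study at six-monthly intervals", and adds: "One ACCHS per state will begin the implementation phase at a time". The footnote to Table 2 says that "6 monthly collection of data will continue from baseline to 36 months". Sample size gives one ICC, 0.01, and no correlation between audits within a service.

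**The concern.** In a stepped wedge the intervention effect is read from service-by-audit cells, by comparing audits before and after crossover within services and across services at the same audit. The primary outcome counts clinic activity: screening, asking about cognition, ordering tests. Such activity can rise or fall for a whole service at one audit and then return. A random intercept absorbs a lasting difference between services, and a random slope absorbs a steady drift. Neither absorbs an irregular swing.

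If the model has only those two terms, the clients in a cell are taken as independent around the service's line. Chance movement of a service near its crossover is then measured against too small a standard error and may be declared a programme effect. This can happen when the programme does nothing, and it does not require effects to differ between services.

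**Working it through.** **Inputs from the article.** 12 services; one per state at each step, so 3 sequences of 4 services; audits at 0, 6, ..., 36 months, so 36/6 + 1 = 7 audits and 12 × 7 = 84 cells; ICC 0.01; 50 clients per cluster on average (55 with drop-outs); 3% versus 10%; α = 0.05.

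**The plan's own figures reproduce.** With p̄ = 0.065, n per arm = [1.96√(2 × 0.065 × 0.935) + 0.8416√(0.03 × 0.97 + 0.10 × 0.90)]² / 0.07² ≈ 193.5, rounded up to 194, so 388 in all. The design effect is 1 + 49 × 0.01 = 1.49, and 388 × 1.49 ≈ 578. Dividing by 0.9 gives about 643, covered by 12 × 55 = 660. This calculation does not separate lasting from audit-specific variation.

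**Assumptions.** Let CAC be the share of between-service variance that persists across audits, so that 1 − CAC is audit-specific. The article gives no value; I use 1.0, 0.8 and 0.5. An ICC of 0.05, base rates of 6.5% (midway between 3% and 10%) and 20%, fixed audit effects and first intervention audits at 2, 3 and 4 are also assumed. Clients are simulated as independent across audits, although the audits link the same people; this isolates the mechanism.

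**Hand approximation.** With m clients per cell, the variance of a cell mean around the service's level is understated by about 1 + (m − 1) × ICC × (1 − CAC). The true size of a nominal 5% z-test is then 2[1 − Φ(1.96/√inflation)]. With m = 55:

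| ICC | CAC | Inflation | Approximate size |
|---|---|---|---|
| 0.01 | 0.8 | 1 + 54 × 0.01 × 0.2 = 1.108 | 6.3% |
| 0.01 | 0.5 | 1 + 54 × 0.01 × 0.5 = 1.27 | 8.2% |
| 0.05 | 0.8 | 1 + 54 × 0.05 × 0.2 = 1.54 | 11.4% |
| 0.05 | 0.5 | 1 + 54 × 0.05 × 0.5 = 2.35 | 20.1% |

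**Simulation, no true effect.** Linear mixed model, 55 clients per cell, 2,000 data sets per row and base rate (simulation error about ±1 point near 5%). Entries are rejection rates in %, at base rate 6.5% / 20%.

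| ICC | CAC | Intercept + slope, z | Intercept + slope, t on 10 df | Intercept + service-by-audit, z |
|---|---|---|---|---|
| 0.01 | 1.0 | 4.5 / 5.0 | 2.6 / 2.8 | 3.6 / 4.4 |
| 0.01 | 0.8 | 5.7 / 5.9 | 3.3 / 3.2 | 4.2 / 4.5 |
| 0.01 | 0.5 | 8.2 / 8.4 | 5.0 / 4.8 | 4.8 / 5.5 |
| 0.05 | 1.0 | 4.4 / 4.9 | 2.4 / 2.8 | 3.5 / 4.4 |
| 0.05 | 0.8 | 14.4 / 11.3 | 10.1 / 7.5 | 4.7 / 5.1 |
| 0.05 | 0.5 | 23.2 / 19.0 | 18.2 / 14.2 | 4.8 / 4.9 |

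A separate set of runs (50 per cell, 600 data sets per cell of the grid, z-test) agrees. With 20% to 50% of the between-service variance audit-specific, the slope model rejects 5.3% to 7.7% at ICC 0.01 and 10.5% to 18.7% at ICC 0.05; the service-by-audit model rejects 4.8% to 6.0%.

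**Logistic check.** ICC 0.01, base rate 6.5%, likelihood-ratio test, 1,500 data sets, CAC 1.0 / 0.8 / 0.5: the slope model rejects 6.5 / 7.9 / 9.7%, the service-by-audit model 6.3 / 7.1 / 7.5%. About 1.5 points of excess are present with no audit-specific variance and are shared by both models. They come from large-sample tests with 12 clusters. At CAC 0.5 the missing term accounts for about 9.7 − 7.5 = 2.2 points.

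**The case against.** The strongest objection is that the sentence can be read another way. Time nested within service could mean a categorical audit effect with a single variance. That is the service-by-audit effect asked for here, and on that reading there is no defect. The possibility stands, but the sentence does not say so, and a random coefficient on time ordinarily means a slope. If it means categorical coefficients with an unrestricted covariance, there are 7 × 8/2 = 28 parameters to estimate from 12 services, which is not workable.

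Second, this is a condensed article, several configurations are planned, and their details lie in a source and perhaps an analysis plan not shown. That also stands in part: an unstated reference distribution is not a fault in itself, and the z-test is my assumption. With a t reference on 10 degrees of freedom, the slope model stays at or below 5% at ICC 0.01. At ICC 0.05 with audit-specific variance it still rejects about 7% to 18%. The random part, however, is stated text.

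Three stronger inferences are tempting and are not supported:

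- A reader might take the commoner components of the outcome to make matters worse. At ICC 0.01 and CAC 0.5 the linear model gives 8.2% at a 6.5% base rate and 8.4% at 20%. The large rates come from the assumed ICC of 0.05.
- A reader might cite changing auditors as a documented source of swings. The article says "Audits will be completed either by trained research assistants or ACCHS staff, depending on each service’s preferences", which describes a difference between services that the intercept absorbs, not a change from one audit to the next.
- A reader might conclude that only a re-randomisation p-value will do. It is one sound option among several.

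**Conclusion.** The concern holds conditionally. If the random time effect is a linear slope and services vary irregularly between audits, the stated model understates the standard error and the type I error can exceed 5%. It cannot be said that it does exceed 5%: the article gives no audit-specific variance, names no primary model, and leaves the form of random time open.

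At the plan's ICC the inflation is none to modest: about 5% to 8% in a linear mixed model with a z-test and up to about 10% in logistic fits, part of it due to the small number of clusters. At an assumed ICC of 0.05 it is about 10% to 23% when 20% to 50% of the between-service variance is audit-specific. The approximation also shows the inflation growing with the number of clients per cell, and 55 per service is a minimum. The change is worth making because it is cheap and removes the dependence on an unknown variance.

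**What to change.** State under Analysis that every model configuration includes a service-by-audit random effect, with one variance component, beside the service intercept. Say whether a linear slope is kept as well; that combination was not simulated here.

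State also a reference suited to 12 clusters. Two options:

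- A t reference with cluster-based degrees of freedom, for example 12 − 2 = 10. In the linear model with the service-by-audit term this rejected 2.2% to 3.0%, so it is cautious. It was not tried with the logistic fits.
- A within-state re-randomisation test, as the primary or a supporting p-value. If the order of the three services was drawn separately in each state, there are 3! = 6 orders per state and 6⁴ = 1,296 allocations. The permutations must follow the randomisation actually used. In null simulations of 2,000 data sets per scenario this test rejected 4.4% to 5.1%, and it kept about 94% power for an immediate change from 3% to 10% at ICC 0.01.

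The term alone is not enough in logistic fits: with large-sample tests 6.3% to 7.5% remained at ICC 0.01, so both parts are needed. No new data are required. The cost is a little more analysis work and a somewhat wider interval.

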#### Sample size

Previous work in the Kimberley (confirmed by work in NSW) found that in Aboriginal and Torres Strait Islander communities, based on community screening, the true prevalence of dementia in people aged 45 years and over was approximately 10%, and the prevalence for cognitive impairment without dementia was also approximately 10% [5, 45]. Hence, the true prevalence of dementia or cognitive impairment in the relevant population is 20%. In the Kimberley, only 38% of those with dementia and only 3% of those with cognitive impairment had been diagnosed by primary health care practitioners. Moreover, the fraction of dementia cases identified by primary care in this work was likely to be higher than in standard practice as many of those with diagnosed dementia had been identified as part of previous research, with primary care practitioners subsequently notified. Therefore, we assume that no more than 15% of individuals with cognitive impairment or dementia are currently identified by primary health practitioners. The initial prevalence based on detection in primary care will be 15% of 20%, i.e. 3%. At a minimum, the study intervention should enable practitioners to identify at least half (50%) of the primary care patients with dementia or cognitive impairment. This would increase the prevalence based on detection in primary care to 50% of 20%, i.e. 10%. If an intraclass correlation of 0.01 and an average cluster size of 50 individuals is assumed, then the design effect will be 1.49. If the study was an individually randomised trial and we wished to detect an increase in the identification of cognitive impairment and dementia from 3 to 10% then the sample size would need to be at least 388 people (α = 0.05, power = 0.8). Therefore, the sample size required for this cluster randomised study will be 578 (388 × 1.49). Allowing for 10% drop-outs we plan to recruit 12 clusters of at least 55 people each, a total sample size of at least 660 individuals. Secondary outcomes compare the effect of earlier detection on scales of depression and stress and this sample size also has adequate power for these scales. We expect approximately 18 cases to be detected in the control period and 60 in the intervention period. The average cluster size will be 6.5 and assuming an ICC of 0.01, the design effect will be 1.055. Thus, our effective number of control cases will be 17 (18/1.055) and intervention cases 57 (60/1.055). Based on the variation found on the longitudinal data of carer strain in the Kimberley, our proposed study will provide over 80% power to find any clinically important effects.

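### The sample size uses a parallel-group cluster design effect for a stepped-wedge trial, so the stated 80% is not this design's power; it is probably conservative

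*Protocol article*

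**What the plan says.** The Design section commits to a "stepped wedge cluster randomised controlled trial design with 12 clusters (ACCHSs) across four states of Australia". Under Setting there is "recruitment of three ACCHS in each state", "the ACCHSs will enter the implementation phase of the study at six-monthly intervals", and "One ACCHS per state will begin the implementation phase at a time". That gives three sequences of four services. The footnote to the data collection timetable (Table 2) says "6 monthly collection of data will continue from baseline to 36 months", which is up to seven audits; three steps need at least four. The Medical record audit section gives each client an identifier so that audits can be linked.

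The Sample size section assumes detected prevalence rising from 3% to 10%, an intraclass correlation (ICC) of 0.01 and an average cluster size of 50. It takes 388 people for an individually randomised comparison at α = 0.05 and power 0.8, and continues: "Therefore, the sample size required for this cluster randomised study will be 578 (388 × 1.49". A 10% drop-out allowance leads to 12 services of at least 55 people, 660 in all. Later in the same section: "We expect approximately 18 cases to be detected in the control period and 60 in the intervention period".

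**The concern.** The factor 1 + (m − 1) × ICC describes a trial in which each cluster stays in one arm and is measured once. A stepped wedge differs in three ways that the calculation leaves out:

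- each service contributes data under both conditions, which gains information;
- the comparison is partly confounded with calendar time, and adjusting for time loses information;
- the same clients may be measured repeatedly.

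The net effect can go either way. It depends mainly on how many clients are audited per service at each cycle, and the section does not say whether 55 is per audit, one cohort audited repeatedly, or a total. A reader therefore cannot tell from the stated 80% whether the audit plan is adequate or larger than needed. The figure of 55 is also a service eligibility criterion under Inclusion criteria, so it affects which services can join.

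**Working it through.** **1. The protocol's own figures (Sample size section).** Two-sided 0.05, power 0.80, pooled variance under the null, mean proportion 0.065:

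n per group = [1.96 × √(2 × 0.065 × 0.935) + 0.842 × √(0.03 × 0.97 + 0.10 × 0.90)]² / 0.07² = 193.5, rounded up to 194, so 388 in total.

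Design effect = 1 + 49 × 0.01 = 1.49. 388 × 1.49 = 578. 578 / 0.9 = 643, which 12 × 55 = 660 covers. Taken as a parallel two-arm cluster trial, 578 people give power 0.801. The arithmetic is right for that design.

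**2. Stepped-wedge calculation.** Generalised least squares on cluster-period means, with power = Φ(0.07 / SE − 1.96).

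- From the protocol: 12 services, 3 sequences of 4, 3% vs 10%, ICC 0.01.
- Assumed: random cluster intercept, fixed period effects, variance at the mean proportion (0.065 × 0.935), and 4 or 7 analysed audits.

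| Meaning of 50–55 | Audits | Clients per service per audit | SE | Power |
|---|---|---|---|---|
| Different clients at every audit | 4 | 50 / 55 | 0.0174 / 0.0166 | 0.981 / 0.988 |
| Different clients at every audit | 7 | 50 / 55 | 0.0165 / 0.0157 | 0.989 / 0.994 |
| Total, spread over audits | 4 | 12.5 / 13.75 | 0.0321 / 0.0308 | 0.587 / 0.623 |
| Total, spread over audits | 7 | 7.1 / 7.9 | 0.0413 / 0.0394 | 0.396 / 0.427 |

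If the same 50–55 clients are re-audited, with an assumed within-client correlation of 0.2 to 0.8, power is 0.99 or higher. With four audits, 80% power needs about 22 clients per service per audit: 22 × 4 × 12 = 1,056 observations.

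**3. Which reading the text favours.**

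- Linking successive audits serves no purpose if each client is audited once.
- A drop-out allowance implies follow-up.
- The 18 and 60 expected cases are 3% and 10% of 12 × 50 = 600, so the same 600 people are counted under both conditions. A two-group total of 578 would instead put about 289 in each.

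All three point to 50–55 clients at every audit or one re-audited cohort.

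**4. Sensitivity.** With 50 per audit, four audits and ICC 0.01, letting the between-period cluster correlation fall from 1.0 to 0.4 moves power only from 0.981 to 0.965. At larger ICCs it matters: ICC 0.05 with cluster autocorrelation 0.6 gives 0.803, and ICC 0.10 with 0.5 gives 0.569.

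**The case against.** The strongest reply is that 660 is safe. On the reading that the text supports, power is well above 80%, so the simple formula errs on the cautious side and no client, visit or analysis changes. This stands, and it limits the point to the stated power and the undefined 55. It does not make the calculation correct: the section does not present 1.49 as a deliberate approximation, and the result is cautious only under a reading that the section never states.

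A reader might infer from the 40–62% figures that the trial is underpowered. The documents do not support that. Those figures need 50–55 clients to be divided across audits, against the linkage, the drop-out allowance and the case counts. They also depend on fixed period effects, whereas the Analysis section specifies a random time coefficient and up to four model configurations. Without period effects, 50 clients spread over the audits would give 0.92 (4 audits) or 0.88 (7 audits). Adjusting for calendar time is sound practice in a stepped wedge, but the low figures remain model-dependent, and with 7 to 14 clients per cell the normal approximation is rough.

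A reader might also see a flat contradiction between 578 and the 18/60 counts. Those counts open the secondary-outcome calculation (78 / 12 = 6.5 cases per cluster) and count people in both periods, as a stepped wedge does. They are better taken as evidence of the intended design.

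Nor is the 3% control rate shown to be wrong. The Kimberley fractions give 0.38 × 10% + 0.03 × 10% = 4.1%, but the section explains why it goes lower: detection there was raised by earlier research.

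**Conclusion.** The point holds as a mismatch between design and formula. The 578 and the 80% are correct for a parallel cluster trial measured once and are not properties of the stepped wedge described. At 3% vs 10% and ICC 0.01, power is about 98–99% on the better-supported reading and 99% or more for a re-audited cohort. It falls below 80% only if 50–55 is a total spread over the audits.

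The stated power is therefore wrong and probably conservative; the trial is not shown to be underpowered. This rests on an assumed variance model, on 4 to 7 analysed audits, and on within-client and between-period correlations that the article does not give. The cohort figures are only indicative, because new documentation, once made, cannot be undone. The margin also depends on the ICC of 0.01: the higher ICCs with decaying cluster correlation shown above bring power to 80% or lower even with 50 clients per audit.

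**What to change.** Replace the 1.49 step with a stepped-wedge calculation that states: three sequences of four services; the number of audits analysed; clients per service per audit; the time adjustment to be used; and ranges for the ICC, its decay between periods and the within-client correlation. Say in one sentence whether 55 is per audit, one re-audited cohort or a total per service. Restate the resulting power. A 4.1% control rate is at most an optional sensitivity check.

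No extra clients are needed. The cost is a few hours of statistician time, revised sample-size wording and a changed power figure.
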